### 2.4. Interventions

#### 2.4.1. Control Group

The Control Group and the Intervention Group will perform the physical exercise protocol for 16 weeks (twice a week) in Health Units, in partnership with trained physiotherapists and physical educators from primary health care and the assistance of the research team. The program will consist of a 10 min warm-up, 20 min balance and gait physical exercises, including how to get up after a fall, 20 min muscle strength physical exercises for the trunk and lower limbs with a functional focus, and 10 min cool-down (muscle stretching and breathing physical exercises), totaling 60 min per session and 120 min per week [13,14]. The physical exercises will have moderate intensity and individualized progression every 3 weeks. Moreover, the participants from the Control Group will be encouraged to maintain their routine and will receive monthly telephone calls for general health guidance.

#### 2.4.2. Intervention Group

Besides the physical exercise protocol, the Intervention Group will be submitted to a case management intervention for 16 weeks, once a week, consisting of the following:

First week: Multidimensional assessment with all potentially modifiable falls risk [3] at the volunteer’s home, at a previously scheduled time;

First–second weeks: Explanation of the risks identified by the case managers to the older person and their families, when appropriate, preferably by video call through the platform of the person’s choice (Google Meet or WhatsApp video) or by telephone at a previously scheduled time. If the volunteer agrees to make the video calls, a video tutorial and PDF will be sent, if necessary;

Second–third weeks: Suggestion of interventions based on the identified risk factors, motivational interview, and individual preferences. The risk factors with the highest intervention priorities will be listed together with the person, preferably by video call or by telephone at a previously scheduled time;

Second–third weeks: Creation of an individualized falls intervention plan, prepared together with the older person, considering treatments for priority falls risks, personal preferences, and available resources, to be carried out preferably by video call or by telephone at a previously scheduled time;

Third–sixteenth weeks: Implementation of the plan by the volunteer, case manager, and other care providers, such as guidance and recommendations, communications with providers, and referrals to specialized programs (through knowledge/understanding of the person’s care network and other community support resources, seeking contacts and information about referrals to programs and subsequent sending of letters, e-mails and/or phone calls with information about the case, in agreement with the person, the family and the health professional/service responsible). If there is a delay in care at the reference service, other strategies will be offered for the identified risk factor, in addition to health education about it and facilitation of communication and integration of services. Monitoring of the plan and its revision, if necessary. Monitoring will be carried out by video calls or phone calls. At this stage, it will be determined whether the person is having difficulty implementing any action, what assistance could be provided, and what modifications could be made (Figure 3) [8].

All cases will be discussed weekly with case managers (undergraduate students in Gerontology at UFSCar and/or gerontologists) and two professionals who are specialists in the area. The case manager must act as an advocate for the older person, their family, and their social support network, in order to defend their interests, empower self-care, autonomy, and independence, facilitate communication with service providers, and coordinate care throughout the network. In this sense, the case managers will receive remote training over 6 months, with real and fictitious case studies.

Furthermore, to facilitate the future implementation of the intervention based on case management with a focus on fall prevention in the health sectors, a partnership was established with the Institute of Mathematics and Computer Science of the University of São Paulo, São Carlos campus (ICMC-USP), Brazil, to create a free Web-based and interactive software for case management interventionists to optimize the management and support their decision-making processes throughout the intervention. The first model was revised in June 2025, after weekly meetings with the creators. The second model will be created by the end of 2025. We expect to have a third and final model in 2026. After that, our research group and the health units will have the opportunity to use the model for case management. We intend to collect data on satisfaction and usability among health professionals that work with falls prevention and health managers.

Thus, we seek to implement strategies for primary health care by checking health data, providing feedback to the older person and their family members, and reporting to the health unit (Secretariat and Ministry of Health) all information regarding the patient. Also, we intend to promote recommendations to achieve long-term adherence and health education, and to investigate the feasibility and applicability of using the software for case management and investigate the costs of implementing the program.

After 16 weeks of intervention, participants in both groups will receive a home physical exercise booklet and will be instructed to follow it until the end of 12 months of follow-up. In addition, participants in the Intervention Group will receive a guidance manual on how to manage the main risk factors for falls and will be guided to maintain the agreed recommendations in case management.

### 2.5. Outcome Measures

Participants will be instructed to wear comfortable clothing and appropriate shoes and use hearing and/or visual aids when necessary. The assessment will be performed at baseline, after 16 weeks of intervention, after 6-month follow-up, and after 12-month follow-up. The evaluators will be blinded and properly trained. All tests will be explained in a clear, simple, and objective manner to the participants. The assessments will be performed at the participants’ homes, if possible, in an environment with minimal noise and distractions.

### 2.6. Primary Outcome Measures

Primary outcome measures include falls data and potentially modifiable risk factors for falls. A fall will be defined to the volunteer as “an event that results in a person inadvertently coming to rest on the ground or other level below and it is not a consequence of a violent blow, loss of consciousness, sudden onset of paralysis or epileptic seizure” [15]. The number of falls and their consequences (lesion, fracture, death, fear of falling, functional difficulty, expenditure, and others) will be monitored in both groups for 12 months through monthly telephone calls, with third party verification to reduce recall bias. Table 1 presents assessments of risk factors for falls.

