The sample size was calculated based on the primary outcome measures (potentially modifiable risk factors for falls, especially motor risk factors). The sample size was calculated using the statistical program G*Power 3.1, assuming (1) the purpose of identifying the effectiveness of risk factors after 16 weeks of intervention; (2) the test used (two-way ANOVA, considering group and time effects, with Bonferroni test to control type I error due to multiple primary outcomes); (3) the main measure; (4) type I error at 5%; (5) statistical power at 80%; and (6) an effect size of 0.25, a minimum of 28 people should constitute the total sample. Furthermore, to verify the sociodemographic and clinical factors that influence adherence and satisfaction, the rule of at least 10 cases of the outcome (success or failure, depending on which is rarer) was used for each independent variable used in the logistic/linear regression model [12]. Thus, considering an adherence of 80% based on a previous study by the research group [9] and the use of univariate regression analyses, a minimum of 50 people should constitute the total sample. With the chance of losing 20% of participants, a sample of 60 people in total is estimated.

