### 2.9. Statistical Analysis

A descriptive analysis will be performed. A significance level of α = 0.05 will be adopted for all analyses and the SPSS (22.0) software will be used to perform the statistical tests. The analysis will be performed by intention to treat. The Kolmogorov–Smirnov normality test will be applied to all continuous variables to verify data distribution. To compare groups regarding clinical and sociodemographic characteristics, the chi-square association test for categorical variables, the independent *t*-test for continuous variables with normal distribution, and the Mann–Whitney test for continuous variables with non-normal distribution will be used.

If the normality hypothesis is rejected, the z-score calculation will be performed to standardize continuous data. Volunteers will be classified as having no clinical improvement when the GRCS score is between −7 and 0, moderate improvement between 1 and 3, and great improvement between 4 and 7 after the intervention. The anchoring technique will be used to estimate the minimum clinically relevant difference, using the GRCS as an anchor. Correlations between the GRCS and performance changes of each test will be conducted. The Receiver Operating Characteristic (ROC) analysis will be used to compare the values of each test between volunteers who improved and did not improve according to the GRCS. Through this method, the cutoff score, specificity, and sensitivity of each test will be analyzed [15].

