To verify the effectiveness of the interventions, the chi-square association test will be used for categorical variables. About the use of fNIRS, a pilot study was conducted before data collection, and the fNIRS signal demonstrated good quality across the targeted channels and participants, with minimal signal loss or saturation. This assured us the feasibility and reliability of the measurements. Regarding the data workflow, motion artifact control, and ROI selection, at this stage, the specific fNIRS data analysis is still ongoing, and a preregistered analysis plan has not yet been developed. We intend to finish this step until the end of 2025. Using the fNIRS, the digitizer data will be entered into the NIRS-SPM software package (v. 4), implemented in MATLAB 2017 (Natick, MA, USA). The fNIRS data will be preprocessed using custom MATLAB algorithms [51]. For quantitative variables, the two-way ANOVA test will be used to verify the interaction between groups and evaluations, with Bonferroni test to control type I error due to multiple primary outcomes. If an interaction is identified, simple main effects analyses will be performed, with adjustments for multiple comparisons (Bonferroni). To verify the proportion of individuals who did not suffer any fall episode during the 12-month follow-up (“proportion of people who did not have the first fall” and “proportion of people who did not have the second fall”), the Kaplan–Meier analysis will be used.

To verify adherence and satisfaction with interventions and sociodemographic and clinical factors that influence them, descriptive analyses of quantitative and qualitative data will be used, using the MAXQDA2022 software for coding and categorization. The excerpts of the responses will be separated into segments containing the ID of each volunteer and their corresponding code. After coding, the segments obtained will be organized using Bardin’s content analysis [52]. Furthermore, simple linear regression analysis will be used to verify possible influences of adherence (frequency) and satisfaction (score). Also, descriptive analyses and the chi-square association test will be used.

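### No single primary outcome or time point is named, and the Bonferroni step has no stated family and covers only the ANOVA outcomes, so overall type I error is not controlled

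*Protocol article*

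**What the plan says.** Section 2.6 of the protocol article defines the primary set: "Primary outcome measures include falls data and potentially modifiable risk factors for falls". It then refers the reader to a table: "Table 1 presents assessments of risk factors for falls". Table 1 has 16 risk-factor rows and, by hand count, about 44 instruments or items. EuroQol-5D is among them but is also used under section 2.7 (secondary outcomes). Functional near-infrared spectroscopy (fNIRS) is there too, and section 2.9 says of it that "a preregistered analysis plan has not yet been developed".

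Section 2.5 schedules a baseline and three later assessments (16 weeks, 6 months, 12 months). Section 2.6 follows falls for 12 months. No time point is called primary.

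The sample-size paragraph in section 2.3 refers to "potentially modifiable risk factors for falls, especially motor risk factors" and lists, among its assumptions, "3) the main measure; (4) type I error at 5%; (5) statistical power at 80"%. No instrument is identified. The stated result is a minimum of 28 people at effect size 0.25, for effects after 16 weeks. A separate regression rule raises this to 50, and an allowance for 20% loss brings it to 60.

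On error control, section 2.9 says "A significance level of α = 0.05 will be adopted for all analyses". Sections 2.3 and 2.9 add a Bonferroni test for multiple primary outcomes, both times attached to the two-way ANOVA for quantitative variables, without the number of tests. For the chi-square tests of effectiveness and the Kaplan–Meier analyses of first and second fall, no adjustment is mentioned.

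**The concern.** The trial is declared a superiority trial (section 2.1), so a reader must be able to tell in advance which result decides whether case management adds to exercise. Here that is not fixed. A favourable result on falls or on any of many risk-factor measures, at any of three later time points, could be reported as a positive primary outcome.

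The Bonferroni sentence does not close the gap. Without a stated family the per-test level is unknown, and outcomes analysed by chi-square or Kaplan–Meier fall outside it. The choice of family also matters for power: a short list costs little, while a family as wide as Table 1 would need more people than the minimum given in section 2.3.

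**Working it through.** **1. The plan's own figure.** Section 2.3 gives 28 people (f = 0.25, alpha 5%, power 80%). The number of measurements m and the correlation rho between them are not stated, so both are assumptions here. For the group-by-time interaction with two groups and sphericity, λ = f²·N·m/(1 − rho), with df = (m − 1) and (N − 2)(m − 1).

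- alpha 0.05, m = 3, rho = 0.5: λ = 0.0625 × 28 × 3/0.5 = 10.5; power 81.2%.
- alpha 0.05, m = 2, rho = 0.6: λ = 0.0625 × 28 × 2/0.4 = 8.75; power 81.3%.
- alpha 0.025 (a family of two), m = 4, rho = 0.5: λ = 0.0625 × 28 × 4/0.5 = 14; power 81.0%.

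The figure of 28 therefore reproduces with or without a Bonferroni division and does not reveal which family, if any, was intended.

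**2. False positives if K outcomes are each tested at 0.05.** Under independence the chance of at least one is 1 − 0.95^K. For the correlated case I used two-sided normal tests with a common assumed correlation r, integrating numerically over a shared factor.

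| K | independent | r = 0.3 | r = 0.5 |
|---|---|---|---|
| 16 (Table 1 rows) | 56% | 48% | 37% |
| 44 (Table 1 items) | 90% | 77% | 59% |

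**3. Power per outcome with Bonferroni over K outcomes.** Same formula as step 1, f = 0.25, rho = 0.5 assumed. Per-test alpha is 0.05/2 = 0.025, 0.05/16 = 0.0031 or 0.05/44 = 0.0011. Completers: 60 × 0.8 = 48. Entries are for m = 2 / 3 / 4.

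| K | N = 28 | N = 48 |
|---|---|---|
| 2 | 61 / 72 / 81% | 87 / 94 / 98% |
| 16 | 30 / 43 / 55% | 64 / 80 / 90% |
| 44 | 19 / 31 / 43% | 50 / 70 / 84% |

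**4. Falls.** Section 2.3 contains no calculation for falls. As an indication, take a negative binomial comparison over 12 months with control rate μ₀ = 1.5–2 per person-year and dispersion k = 1–1.5, all assumed. Var(log RR) = (1/μ₀ + k)/n + (1/(μ₀·RR) + k)/n. The rate ratio detectable with 80% power at two-sided 5% solves −log RR = (1.960 + 0.842)·√Var.

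| n per arm | μ₀ = 1.5, k = 1 | μ₀ = 1.5, k = 1.5 | μ₀ = 2, k = 1 | μ₀ = 2, k = 1.5 |
|---|---|---|---|---|
| 24 (48/2) | 0.28 | 0.23 | 0.31 | 0.27 |
| 30 (60/2) | 0.33 | 0.29 | 0.37 | 0.32 |

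The range is 0.23–0.37, that is, a reduction in the fall rate of 63–77%. The article plans Kaplan–Meier rather than a rate model, so this shows the order of magnitude and not the power of the planned analysis.

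**The case against.** Five points can be made for the plan.

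- A reader might infer that alpha 0.05 for all analyses contradicts Bonferroni. It does not: 0.05 can be the family-wise level that Bonferroni divides. What stands is that the family is neither counted nor extended beyond the ANOVA.
- A reader might take every Table 1 item as primary. Section 2.6 limits the primary set to potentially modifiable factors and says only that the table presents their assessments. Items such as living alone may simply feed the care plan in section 2.4.2. The counts of 16 and 44 are therefore illustrations of how wide the set could be. The article still does not say where it ends.
- A reader might conclude that a false positive is nearly certain. The figures in step 2 assume no adjustment at all, whereas the plan commits to Bonferroni for quantitative outcomes. Independence is also unrealistic, because several cognitive tests sit within one examination and gait speed and sit-to-stand sit within one battery.
- A reader might say that power collapses under Bonferroni. That fits 28 people. At 48 completers it depends on the number of measurements, and with four of them power remains 84–90%.
- The counting of tests is commonly left to an analysis plan, which is not shown. That is fair for the mechanics. The choice of primary outcome, however, is made in this article and made too broadly; an analysis plan could narrow it only by overriding section 2.6.

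**Conclusion.** The concern holds in this form: the primary set is open-ended, no time point is primary, the measure behind the sample size is not named, and multiplicity control is undefined and incomplete. Overall type I error across the declared primary outcomes is therefore not controlled.

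The size depends on how many outcomes count and how correlated they are, neither of which the article fixes. At one extreme (16–44 outcomes, no adjustment) the chance of a false positive is 37–90%. At the other (Bonferroni over the same numbers) power is 19–55% at 28 people and 50–90% at 48 completers, given f = 0.25 and rho = 0.5. For falls, only a very large effect could be detected reliably under the assumed rates.

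This should be corrected before comparative data are seen, because afterwards any choice of deciding outcome can be questioned.

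**What to change.** - In section 2.6 and the registry entry, name one primary outcome and one time point. The sponsor's own main measure at 16 weeks fits the existing size calculation. A short fixed list, such as that measure plus falls with alpha split between them, is equally valid. With two outcomes at 0.025 each, the main measure keeps 87% power at 48 completers even with two measurements (step 3).
- Which outcome is chosen is for the sponsor. Both arms receive the same exercise programme, so a motor measure is not automatically where case management should show most.
- Identify the main measure in section 2.3.
- Make the remaining Table 1 measures secondary without confirmatory claims, and fNIRS exploratory.
- In section 2.9, state that 0.05 is the family-wise level for the named primary outcome or outcomes, whatever test is used.
- If falls are not sized for, report them with a confidence interval and make no power claim.

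The cost is wording in the protocol and registry, with no new data or participants. The downside is that only the named outcome or outcomes can carry the confirmatory claim.

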Finally, we will include the economic variable in the analysis, which will be measured by the incremental cost-effectiveness ratio. It will be calculated based on the difference between the total cost of the IG and the GC. In addition to this variable, we will also analyze the use of health services, measured based on the results of the EuroQol-5D. With the aim of comparing the effects in five dimensions, e.g., mobility, self-care, usual activities, pain/discomfort, and anxiety/depression, obtained in interventions and with scores ranging from 1 to 3 for each item, this instrument is widely used in cost-effectiveness studies [39].

### 2.8. Randomization and Blinding

Participants will be randomly assigned to the Intervention or Control group with a 1:1 allocation using computer-generated randomization software with blocks of random sizes (2, 4, 6). All allocation concealment mechanisms will be conducted by other independent researchers. An independent researcher will open sequentially numbered, opaque, sealed containers with printed randomization numbers and the corresponding group. The researcher then will give information about treatment allocation to the volunteer and care manager staff.

Assessments will be conducted by trained assessors blind to treatment allocation. Due to the nature of the intervention, neither participants nor care managers can be blinded to allocation. They are strongly oriented not to disclose the allocation status of the participant during assessments. The blinded researchers will not have access to information about the allocation until the assessment ends (Figure 4).

### 2.9. Statistical Analysis

A descriptive analysis will be performed. A significance level of α = 0.05 will be adopted for all analyses and the SPSS (22.0) software will be used to perform the statistical tests. The analysis will be performed by intention to treat. The Kolmogorov–Smirnov normality test will be applied to all continuous variables to verify data distribution. To compare groups regarding clinical and sociodemographic characteristics, the chi-square association test for categorical variables, the independent *t*-test for continuous variables with normal distribution, and the Mann–Whitney test for continuous variables with non-normal distribution will be used.

If the normality hypothesis is rejected, the z-score calculation will be performed to standardize continuous data. Volunteers will be classified as having no clinical improvement when the GRCS score is between −7 and 0, moderate improvement between 1 and 3, and great improvement between 4 and 7 after the intervention. The anchoring technique will be used to estimate the minimum clinically relevant difference, using the GRCS as an anchor. Correlations between the GRCS and performance changes of each test will be conducted. The Receiver Operating Characteristic (ROC) analysis will be used to compare the values of each test between volunteers who improved and did not improve according to the GRCS. Through this method, the cutoff score, specificity, and sensitivity of each test will be analyzed [15].

To verify the effectiveness of the interventions, the chi-square association test will be used for categorical variables. About the use of fNIRS, a pilot study was conducted before data collection, and the fNIRS signal demonstrated good quality across the targeted channels and participants, with minimal signal loss or saturation. This assured us the feasibility and reliability of the measurements. Regarding the data workflow, motion artifact control, and ROI selection, at this stage, the specific fNIRS data analysis is still ongoing, and a preregistered analysis plan has not yet been developed. We intend to finish this step until the end of 2025. Using the fNIRS, the digitizer data will be entered into the NIRS-SPM software package (v. 4), implemented in MATLAB 2017 (Natick, MA, USA). The fNIRS data will be preprocessed using custom MATLAB algorithms [51]. For quantitative variables, the two-way ANOVA test will be used to verify the interaction between groups and evaluations, with Bonferroni test to control type I error due to multiple primary outcomes. If an interaction is identified, simple main effects analyses will be performed, with adjustments for multiple comparisons (Bonferroni). To verify the proportion of individuals who did not suffer any fall episode during the 12-month follow-up (“proportion of people who did not have the first fall” and “proportion of people who did not have the second fall”), the Kaplan–Meier analysis will be used.

To verify adherence and satisfaction with interventions and sociodemographic and clinical factors that influence them, descriptive analyses of quantitative and qualitative data will be used, using the MAXQDA2022 software for coding and categorization. The excerpts of the responses will be separated into segments containing the ID of each volunteer and their corresponding code. After coding, the segments obtained will be organized using Bardin’s content analysis [52]. Furthermore, simple linear regression analysis will be used to verify possible influences of adherence (frequency) and satisfaction (score). Also, descriptive analyses and the chi-square association test will be used.

To address missing data resulting from loss to follow-up, we plan to use multiple imputation methods under the assumption of missing at random and to perform sensitivity analyses using mixed-effects models, which can accommodate unbalanced data and account for intra-individual variability over time. These approaches will help to minimize potential bias associated with missing outcome data.

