## Abstract

**Background/Objectives**: There is a need for randomized clinical trials with higher quality, especially for older people at high risk of falls, with interventions that consider individual needs, comprehensiveness of care, and connection with primary health care. We designed a randomized controlled trial to examine the effects of a case management intervention combined with a physical exercise protocol on risk factors for falls, falls data, adherence, satisfaction, costs, and implementation in community-dwelling older adults with high risk of falls. **Methods**: A minimum of 60 community-dwelling older people with high falls risk will participate in the randomized controlled assessor-blinded trial (MAGIC—v. 2). The trial will be conducted in a regional health department of São Paulo state (Brazil), which includes 6 cities. Participants will be randomized to the Intervention Group (case management intervention based on all individual risk factors for falls identified by a multidimensional assessment, over 16 weeks, once a week, by telephone calls). Both groups will perform a physical exercise protocol based on falls prevention for 16 weeks (twice a week) in Health Units. The assessment will be performed at baseline, after 16 weeks of intervention, after 6-month follow-up, and after 12-month follow-up. Primary outcome measures include falls data and potentially modifiable risk factors for falls. **Discussion**: This study has the potential to facilitate the future implementation of the intervention based on case management with a focus on fall prevention in the health sectors. **Trial registration**: Brazilian Registry of Clinical Trials (ReBEC).

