Another important improvement will be that the assessments will be in-person and not remote, as in the previous protocol the monitoring took place during the COVID-19 pandemic. Furthermore, we hope to identify the minimum clinically relevant difference in tests that assess neuropsychological risk factors for falls and understand the adherence and long-term satisfaction of older people in the intervention.

Since randomized clinical trials are considered the gold standard for evaluating the effectiveness of interventions due to their ability to minimize bias and establish causal relationships between interventions and outcomes, our methodological choice was based on this fact to provide high-level evidence on the effectiveness of our interventions for preventing falls in older adults. In addition, block randomization ensures a balance between groups, and blinding of evaluators reduces detection bias, making the results more robust. Finally, the fact that we conducted the intervention in the primary health care context will allow us to assess not only the effectiveness of the intervention but also the potential implementation challenges that may arise throughout the project, which is extremely important for future implementation of public health strategies.

This study has some limitations that should be considered. For example, the recruitment strategy may favor volunteers who are more motivated or have better access to health services, introducing a potential selection bias. Furthermore, because the intervention involves multiple locations and coordination between different municipalities, logistical challenges, such as participant retention and intervention fidelity, may pose obstacles throughout the study’s development. To this end, the negotiating meetings with the municipalities enabled a more secure alliance between the partners. Despite these limitations, the rigorous design, evaluator blinding, and justification strengthen the study’s internal validity.

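### Each test's MCID cut-off and its accuracy come from one ROC analysis of about 48 to 60 people; under the usual optimising rules the cut-off is imprecise and the accuracy overstated

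*Protocol article*

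**What the plan says.** Section 2.9 (Statistical Analysis) uses the global change rating scale (GRCS) at 16 weeks as the anchor. Participants are graded as "no clinical improvement when the GRCS score is between −7 and 0, moderate improvement between 1 and 3, and great improvement between 4 and 7". An ROC analysis then compares the improved with the not improved on each test, and "Through this method, the cutoff score, specificity, and sensitivity of each test will be analyzed". Section 2.9 does not say how a point on the curve becomes the cut-off.

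The only sample described is the trial's own. The Abstract says "A minimum of 60 community-dwelling older people with high falls risk will participate", and section 2.3 says "With the chance of losing 20% of participants, a sample of 60 people in total is estimated". Neither sample-size calculation in section 2.3 concerns the ROC analysis: one is for an ANOVA and the other is an events-per-variable rule for regression. Table 1 lists many instruments, so the procedure would be repeated many times.

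The MCID is listed under secondary outcome measures (section 2.7). The Introduction presents it as one of the advances of version 2, and the Discussion adds that "we hope to identify the minimum clinically relevant difference in tests that assess neuropsychological risk factors for falls".

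**The concern.** An empirical ROC curve from a few dozen people is a staircase. A rule that picks the best-looking step picks partly on chance, which has two consequences. The chosen cut-off varies widely from sample to sample. The sensitivity and specificity read at that step, in the same people, are higher on average than the same cut-off would achieve in new people. Both occur even when the test is truly related to the anchor.

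At stake is the reliability of the published MCIDs. Such values are reported so that others can use them. A cut-off quoted without its uncertainty, beside flattering accuracy figures, would be trusted more than it deserves.

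**Working it through.** **The plan's own numbers.** The regression rule asks for 10 cases of the rarer outcome. Section 2.3 gives the basis as "considering an adherence of 80% based on a previous study by the research group", so the rarer outcome is 20% and 10 / 0.20 = 50. Then 50 × 1.2 = 60, the stated total. Losing 20% of 60 leaves 60 × 0.8 = 48. The ANOVA figure of 28 is smaller and does not drive the total. The ROC analysis therefore has about 48 completers, or 60 with no loss.

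**Assumptions not in the document.** The correlation between change score and anchor, the share improved, the distribution of change scores and the cut-off rule are all assumed. J is sensitivity + specificity − 1. Optimism is J as reported in the sample minus true J at the same cut-off in the population.

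**Model A: bivariate normal change score and latent anchor.** Base case N=48, correlation 0.4 (AUC about 0.69), 70% improved. Errors are in SDs of change.

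| Method | Cut-off RMSE | Optimism in J |
|---|---|---|
| Maximum sensitivity + specificity | 0.52 to 0.53 | 0.16 |
| Closest to the (0,1) corner | about 0.29 (SD of cut-off) | 0.12 |
| Sensitivity = specificity | about 0.20 | 0.006 |
| Logistic cut-off | 0.16 | at most 0.02 (over the settings run) |

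Under the maximum-sum rule, reported sensitivity and specificity average 0.68 and 0.72, so J = 0.68 + 0.72 − 1 = 0.40. At the same cut-offs the true values are 0.63 and 0.61, so J = 0.63 + 0.61 − 1 = 0.24, and 0.40 − 0.24 = 0.16. The cut-off's 90% sampling range is −1.04 to +0.66 SD. True J at the logistic cut-off is 0.26 to 0.27 across runs.

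Over correlations of 0.3 to 0.5 and 50% to 70% improved, at N=48, the two optimising rules give an RMSE of about 0.25 to 0.60 SD and optimism of about 0.10 to 0.17. The logistic cut-off gives an RMSE of about 0.14 to 0.16 SD.

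**Model B: two normal groups with equal variance, 3,000 replicates.** With AUC 0.70 the group means differ by √2 × Φ⁻¹(0.70) = 0.74 SD, so the best cut-off is 0.74 / 2 = 0.37 SD above the not-improved mean. With half improved:

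| N | Rule | SD of cut-off | 95% range | Reported J | True J | Optimism |
|---|---|---|---|---|---|---|
| 48 | Maximum sum | 0.49 | −0.68 to 1.21 | 0.400 | 0.260 | 0.140 |
| 48 | Closest to (0,1) | 0.29 | −0.20 to 0.94 | 0.384 | 0.278 | 0.106 |
| 48 | Sensitivity = specificity | 0.18 | 0.02 to 0.72 | 0.292 | 0.285 | 0.007 |
| 60 | Maximum sum | 0.48 | −0.61 to 1.23 | 0.382 | 0.262 | 0.121 |
| 60 | Closest to (0,1) | 0.26 | −0.15 to 0.89 | 0.367 | 0.280 | 0.087 |
| 60 | Sensitivity = specificity | 0.16 | 0.06 to 0.68 | 0.287 | 0.286 | 0.001 |

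The two models agree: the size of the problem depends mainly on the cut-off rule, and much less on whether N is 48 or 60.

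**The case against.** The strongest objection is that the deciding input is not in the document. Section 2.9 names no rule, and under a sensitivity = specificity rule the optimism all but disappears. A reader might infer that the reported accuracy is bound to be biased upward. The text does not support that; the bias is conditional on an optimising rule. This part of the objection stands.

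A reader might also infer that clinicians would misclassify many more patients because of the planned method. The figures do not show that. True J is 0.24 at the maximum-sum cut-off and 0.26 to 0.27 at the logistic one, so real classification hardly changes. Most of the misclassification comes from the assumed modest link between test and anchor.

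Third, a condensed article may leave the rule, the intervals and any bootstrap to a fuller document, so their absence is not an error. The point does not rest on that absence. It concerns the stated choice to take cut-off and accuracy from one ROC analysis. An interval would disclose the imprecision of an empirical ROC cut-off without reducing it.

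Fourth, 60 is a minimum. At N=120 the maximum-sum rule still gives an RMSE of 0.41 SD and optimism of 0.09, against a logistic RMSE of 0.10 SD. The multiple imputation planned in section 2.9 adds no independent participants. With change scores rounded to half-SD steps, base-case optimism falls to 0.105, but the SD of the cut-off does not fall (0.59).

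Finally, the logistic cut-off has its own weakness: its target moves with the share improved. Suppose true change is normal with SD 1, the true threshold is 0.50 and observed change has reliability 0.5. The target is then 0.50 + (√2 − 1) × z = 0.50 + 0.414z, where z is the normal quantile of the share improved. That gives 0.28, 0.50, 0.72 and 0.85 at 30%, 50%, 70% and 80% improved. The maximum-sum cut-off shares this target, so the planned method is no better here, but a low RMSE around that target is not the same as accuracy for the MCID.

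**Conclusion.** The concern holds in conditional form. One analysis of about 48 to 60 people sets each cut-off and supplies its accuracy, with no rule named. Under either usual optimising rule at N=48, the cut-off has an RMSE of about 0.25 to 0.60 SD of change, and sensitivity plus specificity is overstated by about 0.10 to 0.17. Under a sensitivity = specificity rule the optimism is near zero and the RMSE is about 0.2 SD. These sizes rest on assumed correlations of 0.3 to 0.5, 50% to 70% improved and normal change scores.

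The harm is imprecise and over-optimistic MCID reporting. It concerns a secondary measurement aim and touches no between-group estimate, so this is a cheap improvement and not a threat to the trial's main comparison.

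**What to change.** In section 2.9, or in the analysis plan that expands it:

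- Estimate each cut-off by logistic regression of improved (yes/no) on the change score, at the change where the predicted odds equal the overall odds, with a bootstrap 95% confidence interval.
- Keep the ROC curve for the AUC. If an ROC cut-off is retained, fix its selection rule before the data are seen.
- Report sensitivity and specificity with bootstrap optimism correction, repeating the whole cut-off selection in each resample.
- Report the share improved beside each cut-off, and label the MCIDs exploratory.

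The cost is a few lines of code and text, with no new data or visits. The downsides should be stated: accuracy figures will look less favourable, the linear-logit assumption must be checked, and the cut-off depends on the share improved, as the maximum-sum ROC cut-off also does.
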